## Abstract

**Background:**

A disturbed circadian rhythm seems to be a causal factor in the occurrence of depressive disorders in patients with Parkinson’s disease (PD). The circadian rhythm can be restored with light. Therefore, Bright Light Therapy (BLT) might be a new treatment option for depression in PD patients.

**Methods/design:**

In this double-blind controlled trial, 84 subjects with idiopathic PD are randomized to either BLT or a control light condition. The BLT condition emits white light with an intensity of 10,000 Lux, while the control device emits dim white light of 200 Lux, which is presumed to be too low to influence the circadian rhythm. Subjects receive 30 min of home treatment twice daily for three months. Timing of treatment is based on the individual chronotype. After finishing treatment, subjects enter a follow-up period of six months. The primary outcome of the study is the severity of depressive symptoms, as measured with the Hamilton Depression Rating Scale. Secondary outcomes are alternative depression measures, objective and subjective sleep measures, and salivary melatonin and cortisol concentrations. For exploratory purposes, we also assess the effects on motor symptoms, global cognitive function, comorbid psychiatric disorders, quality of life and caregiver burden. Data will be analyzed using a linear mixed models analysis.

**Discussion:**

Performing a placebo-controlled trial on the effects of BLT in PD patients is challenging, as the appearance of the light may provide clues on the treatment condition. Moreover, fixed treatment times lead to an improved sleep-wake rhythm, which also influences the circadian system. With our study design, we do not compare BLT to placebo treatment, i.e. an ineffective control treatment. Rather, we compare structuring of the sleep-wake cycle in both conditions with additional BLT in the experimental condition, and additional dim light in the control condition. Participants are not informed about the exact details of the two light devices and the expected therapeutic effect, and expectancies are rated prior to the start of treatment. Ideally, the design of a future study on BLT should include two extra treatment arms where BLT and control light are administered at random times.

**Trial registration:**

This trial was registered on ClinicalTrials.gov on May 17th 2012 (ClinicalTrials.gov Identifier: NCT01604876).

## Background

In patients with Parkinson’s disease (PD), clinically relevant symptoms of depression occur in up to 35 %, with approximately 17 % fulfilling criteria for major depressive disorder (MDD) [1]. Depression has a major impact on overall functioning: depressed PD patients score lower on scales assessing activities of daily living, show a more rapid deterioration of motor and cognitive functioning, and have a higher mortality [2–4]. Depression is highly correlated with insomnia in PD [5–7], both contributing to a reduced quality of life in PD patients and their caregivers [3, 5].

Current treatment options for depression in PD are limited. Antidepressants can have side effects, such as orthostatic hypotension, sedation, and anticholinergic adverse effects, and may aggravate motor symptoms [8–10]. Cognitive behavioral therapy might be effective for the treatment of depression in PD patients, but has not been extensively studied yet [11]. To date, there are no evidence-based treatment options for insomnia in PD, and treatment with hypnotics can have adverse effects [7]. For patients with cognitive dysfunctions, which are common in PD [12], psychotherapy is not a always a feasible treatment option. An alternative treatment for depressive disorders and insomnia in PD patients is therefore needed.

PD patients are prone to desynchronization of the circadian rhythm, due to dopamine deficiency and conflicting input to the SCN [25]. Indeed, a disturbed circadian rhythm is observed in this population. Three studies described a phase advance of melatonin secretion in PD subjects [26–28]. Moreover, a decrease in the amplitude and total amount of melatonin and cortisol secretion has been observed [29, 30]. In another study, the pattern of cortisol secretion was also blunted, but total cortisol concentrations were increased in PD subjects compared to healthy controls [31]. These changes in melatonin and cortisol secretion patterns have also been reported in non-PD subjects with a depressive disorder or insomnia [32–34]. Based on these findings, we hypothesize that a disturbed circadian rhythm is involved in the pathophysiology of depression and insomnia in PD.

### Bright light therapy

Light stimulates melanopsin-containing ganglion cells in the retina, providing the SCN with a ‘daytime’ signal via the retinohypothalamic tract [13]. Bright Light Therapy (BLT) therefore acts as a strong zeitgeber that can restore circadian rhythmicity. Light exposure in the morning advances the circadian rhythm and is effective in the treatment of depressive disorders [35–39], while evening light delays the rhythm and is thought to be more effective in the treatment of early awakening insomnia [32]. Since PD patients have an advanced circadian rhythm [26–28], evening light might be effective in treating not only insomnia, but also depressive symptoms in this population.

In their frequently cited meta-analysis, Golden et al. (2005) concluded that BLT is effective in the treatment of depression in non-PD samples [36]. Recent meta-analyses are more cautious in drawing conclusions on the efficacy of BLT due to limitations of the performed studies, e.g. small and heterogeneous study samples, short treatment duration and lack of a proper placebo condition [35, 37, 38]. The same issue was raised in a Cochrane review on the effects of BLT for treating insomnia in adults aged 60 years and older [40]. However, since treatment effects of pharmacotherapy alone for these disorders are limited, and BLT is a low-cost treatment with a relatively high safety and tolerability [41], it is a treatment option that deserves further research.

In PD, the effects of BLT have been evaluated in two pilot studies [42, 43] and one retrospective, open label study [44]. These studies demonstrated positive effects on depressive symptoms, sleep and motor symptoms. However, depression was not the primary outcome measure in all studies, and all studies had methodological limitations. Therefore, further research on the efficacy of BLT in the treatment of PD patients with a depressive disorder is warranted.

## Methods

This study aims to investigate whether BLT is more effective in reducing depressive symptoms in patients with PD and a depressive disorder, than a control light device. For secondary research purposes, we assess the effects of BLT on insomnia and circadian rhythmicity.

### Study design and procedures

The design of this study is a double-blind randomized controlled clinical trial. An overview of all study procedures is given in Table 1.

### Participants

Participants for this study are recruited throughout the Netherlands by various strategies, including referral by a neurologist, psychiatrist or other medical professional, recruitment through media of various associations involved with PD, and advertisement in a Dutch national newspaper.

Patients are eligible for inclusion when they are diagnosed with idiopathic PD by a neurologist. In addition, they are required to meet criteria of a major depressive disorder as classified by the DSM-IV [45]. Patients with a bipolar disorder are excluded due to the risk of inducing (hypo)mania with BLT [38]. We also exclude subjects with a current psychosis, due to the potential influence on our assessments and the risk of noncompliance. Finally, we exclude patients with a (relative) contraindication for BLT, such as a disorder associated with photosensitization reactions to light, e.g. porphyria, macular degeneration, retinal dystrophy, or lupus erythematosus, or when they have used pharmacological agents with a photosensitizing effect within the past four weeks [20]. Because changes in the use of antiparkinsonian or psychiatric medication might influence assessments, participants have to be on a stable dose of medication for at least four weeks before inclusion. Moreover, subjects and their physicians are asked not to change the medication regime during the treatment phase of the trial, unless this is deemed medically necessary.

### Intervention

The experimental condition consists of BLT with a Brazil® Lightbox (Lumie, Cambridge, United Kingdom). This BLT device emits white, broad spectrum light. During treatment sessions, subjects are instructed to take place in front of the device at a distance of 30 cm, at which the intensity of the light is 10,000 Lux. To create a credible control condition, neutral density filters (Lee Filters, type 209.03ND, Hampshire, United Kingdom) are installed in the light device, so that the experimental and control device have an identical appearance when switched off. These filters reduce transmission uniformly, giving the light a dim white appearance. Subjects are instructed to position themselves at a distance of 40 cm from the control device, at which the light intensity is approximately 200 Lux. At this light intensity, which is lower than in a dimly lit room, no substantial effect on circadian rhythmicity is expected [46].

Subjects in both conditions follow the treatment at home for a period of three months. Subjects use the device both in the morning and the evening. Treatment duration per session is 30 min, which is sufficient to entrain the SCN at an intensity of 10,000 Lux [20]. Timing of the morning treatment session is based on the score on the MEQ [19, 41].

Since evening BLT should be administered at least 90 min prior to bedtime [20], the evening session takes place 9. Five hours prior to the morning BLT, in order to allow eight hours of nighttime sleep. To increase user convenience and compliance, the device is attached to a timer, so that the device switches on automatically at the times set for treatment.

### Outcomes

#### Primary outcome measure

The primary outcome measure of this study is the change in depressive symptoms as regards to baseline, as measured with the 17-item version of the Hamilton Depression Rating Scale (HDRS) [47], from baseline (T0) to the end of treatment (T2).

#### Secondary outcome measures

Our secondary outcome measures are (1) alternative depression measures, (2) subjective and objective quality of sleep, and (3) circadian rhythmicity. Since we are mainly interested in the direct and long-term treatment effects, all outcome measures described below concern the difference between the treatment groups in the change in outcome measures as regards to the baseline value between i) baseline and the end of treatment (T0 to T2) and ii) baseline and the end of follow-up (T0 to T5).Additional depression measures:The change in HDRS-score between T0 and T5 is considered as a secondary outcome measure. As an alternative measure for depression, we use the Geriatric Depression Scale (GDS-30) [48], a self-report instrument. The GDS-30 does not contain items regarding somatic symptoms of depression, and might therefore have a higher diagnostic specificity in PD [48]. As a third depression measure, we assess the proportion of subjects in each treatment group that achieves complete remission at T2 and T5, i.e. fulfilling DSM-IV criteria of a ‘depressive disorder in full remission’, as determined with the Structured Clinical Interview for DSM-IV Axis I disorders (SCID-I) [49].Sleep:Subjective experience of sleep is measured with the Scales for Outcomes in Parkinson’s Disease-Sleep (SCOPA-SLEEP) [50], a validated self-report instrument that contains two subscales: one rating nighttime sleep disturbances and one on excessive daytime sleepiness. Both subscale scores are used as a secondary outcome measure.Sleep patterns are objectified by actigraphy, which is considered to be a valid alternative for polysomnography in the quantitative evaluation of sleep in PD patients [51]. Subjects are asked to wear an actigraphy device (GENEActiv Sleep; GENEActiv, Huntingdon, United Kingdom) on their non-dominant wrist continuously for seven consecutive days. Sleep parameters are calculated in two steps. First, accelerometry data is preprocessed with GENEActive PC software version 2.2, using reports of time of attempted sleep and time of final awakening from the Consensus Sleep Diary (CSD) [52]. Second, the raw GENEActive accelerometry data are converted into Actiwatch counts, as described by Te Lindert et al. (2013), to calculate sleep parameters. The sleep parameters of main interest are total sleep time and sleep fragmentation, i.e. the number of wake bouts per night.
Circadian rhythmicity:In this study, we use salivary concentrations of melatonin and cortisol as markers for the circadian rhythm. At each time point in the study, subjects are instructed to collect saliva at home during a single day, using cotton dental rolls (Salivette®, Sarstedt, Numbrech, Germany). The first saliva sample is taken immediately after waking up, followed by three more samples at an interval of 30 min. In the evening, subjects start hourly collection of samples four hours prior to intended bedtime. Samples are preserved in the refrigerator by the patient, and collected by the researchers one or two days later. They are centrifuged and stored at −80 °C until all samples of one subject that are collected throughout the study can be analyzed simultaneously. The cortisol concentration in the saliva samples is determined by on-line solid-phase extraction liquid chromatography tandem mass spectrometry (XLS-MS/MS), which is preferred over immunoassays to prevent cross-reactivity with other corticosteroids [53]. We will calculate the area under the curve with respect to the ground (AUC_G_) and the area under the curve with respect to the index of salivary cortisol change over time (AUC_I_), as described by Pruessner et al. (2003) [54]. The AUC_G_ is an estimate of the total cortisol secretion throughout the day, whereas the AUC_I_ is a measure of the cortisol awakening response. The AUC_G_ and AUC_I_ of the salivary cortisol concentrations of the morning samples are considered as a secondary outcome measure. We will also report the cortisol concentration in the first saliva sample taken as a measure of the endpoint of pre-awakening increase in cortisol [17]. The melatonin concentrations are assessed in the evening saliva samples using liquid chromatography tandem mass spectrometry (LS-MS/MS). We will calculate the DLMO with the ‘hockey-stick method’, as described by Danilenko et al. (2013) [55].

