#### Efficacy analysis

Analyses will be performed on the Modified-Intent-To-Treat population, which consists of all subjects randomized in the trial who received at least one week of light treatment and provided at least one post-baseline assessment of the HDRS. As a sensitivity analysis, we will compare the baseline characteristics to the Intent-to-Treat population, i.e. all subjects who were randomized in the trial. To assess the effect of treatment duration, we will also assess the effects in the Per Protocol-population, i.e. all subjects who completed the three months treatment duration.

Demographics and clinical characteristics of both the BLT and control group at baseline will be presented with percentages or mean scores with standard deviations. Correlations between continuous variables at baseline will be calculated using Pearson’s correlation coefficients.

The effect of the intervention on the change from T0 to T2, and from T0 to T5, in outcome measures will be assessed using a linear mixed-effects model analysis with assessment visit as the lowest level, and patient as highest level. Time of assessment will be handled as a categorical variable. The effect of the intervention on the outcome measures over time will be modeled by an intervention by time interaction with two degrees of freedom. In all analyses, we will correct for baseline values of the outcome variable. In addition, we will assess whether adding the covariates to the regression model leads to a significant change of the regression coefficient of the condition effect of ≥10 %.

No imputation of missing values will be performed, since linear mixed models handle missing data by placing the data in long format, where the available data of each measurement is nested within persons.

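### Remission (yes/no) falls under a linear mixed model corrected for a baseline value that is the same in every patient, so the correction is empty and remission goes unadjusted for baseline severity

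*Protocol article*

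**What the plan says.** Five statements in the protocol article bear on this point.

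- *Secondary outcome measures*, lead-in: "all outcome measures described below concern the difference between the treatment groups in the change in outcome measures as regards to the baseline value". Remission, determined with the SCID-I, is listed below this as the third depression measure: "we assess the proportion of subjects in each treatment group that achieves complete remission at T2 and T5".
- *Participants*: for entry, "they are required to meet criteria of a major depressive disorder as classified by the DSM-IV".
- *Efficacy analysis*, model: one sentence covers the treatment effect on change over both intervals (to end of treatment and to end of follow-up). Its wording is: "in outcome measures will be assessed using a linear mixed-effects model analysis with assessment visit as the lowest level". No other model is named, and the Abstract also mentions only linear mixed models.
- *Efficacy analysis*, adjustment: "In all analyses, we will correct for baseline values of the outcome variable".
- *Efficacy analysis*, missing data and population: "No imputation of missing values will be performed, since linear mixed models handle missing data by placing the data in long format". The modified intent-to-treat population is made up of randomised patients who "received at least one week of light treatment and provided at least one post-baseline assessment of the HDRS".

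**The concern.** These rules are written for scale scores, yet their scope takes in a binary status. For remission, the promised baseline correction has nothing to work on. The adjustment that would help, for how depressed the patient was at entry, is not offered, because the plan corrects for the baseline value of the same outcome and not for baseline HDRS. Baseline HDRS is not in the *Covariates* list either, which covers medication, environmental light, expectancy and compliance.

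The analyst must therefore depart from the written rule. If nothing is fixed beforehand, the choice between a logistic model, GEE, a linear model and a plain comparison of proportions is left open until the data are in hand.

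The missing-data rule raises a second, smaller issue. Its stated reason is a property of the linear mixed model. If remission is compared as proportions, which is how the outcome is worded, that reason no longer applies. The analysis population requires an HDRS score after baseline but no SCID-I status, so a patient can be in the population and have no remission status at T2.

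**Working it through.** **Figures in the plan.** None is given for remission. The one calculable figure is the HDRS sample size. With d = 0.6, SD 1.0, 80% power and two-sided 5%, n = 2 × (1.960 + 0.842)² / 0.6² = 43.60 per arm. Multiplying by 2 × (1 − 0.6) = 0.8 for the intra-subject correlation of 0.6 gives 34.88, so 35 per arm as stated. Remission does not enter this calculation.

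**Step 1: is the baseline correction estimable?** Code remission as 1 and non-remission as 0. By the entry criterion, the T0 value is 0 for everyone. The stated design has the columns intercept, arm, time, arm × time and baseline. The baseline column is all zeros (under any other coding it is a multiple of the intercept). The rank is 4 with 5 columns, so the baseline coefficient does not exist. Change from T0 equals (status at T2 or T5) − 0, which is the status itself.

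**Step 2: what is left if the empty term is dropped?** A linear mixed model on 0/1 data, in which the arm effect is a risk difference. This was simulated with 42 patients per arm, two visits, a random intercept with SD 1.5 on the logit scale, 20% missing at random per visit, and 400 runs per scenario. The remission rates are assumptions.

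| Assumed rates (control, BLT) | Mean estimate | Rejection rate |
|---|---|---|
| 5%, 5% | 0.002 | 3.8% |
| 10%, 10% | 0.003 | 5.0% |
| 30%, 30% | −0.002 | 7.3% |
| 20%, 45% | 0.248 (true 0.25) | 63.8% |

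The Monte Carlo standard error of a 5% rate is √(0.05 × 0.95 / 400) = 1.1 points, so 7.3% lies about two standard errors above nominal. A second simulation of the same size, with about 10 to 20% missing, also stayed at about 4 to 7%, with or without a T0 row among the outcomes.

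**Step 3: how much does the counting of missing status matter?** Assume observed remission of 40% (BLT) and 20% (control). The 20% loss is the maximum drop-out in *Sample size calculation*.

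| Rule | BLT | Control | Difference |
|---|---|---|---|
| Observed only | 0.40 | 0.20 | 0.20 |
| Missing = not remitted | 0.40 × 0.8 = 0.32 | 0.20 × 0.8 = 0.16 | 0.16 |
| Extreme against BLT | 0.32 | 0.16 + 0.20 = 0.36 | −0.04 |
| Extreme for BLT | 0.32 + 0.20 = 0.52 | 0.16 | 0.36 |

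If loss is unequal and missing counts as not remitted:

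- 30% loss on BLT and 10% on control: 0.40 × 0.7 − 0.20 × 0.9 = 0.28 − 0.18 = 0.10.
- 10% loss on BLT and 30% on control: 0.40 × 0.9 − 0.20 × 0.7 = 0.36 − 0.14 = 0.22.

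**The case against.** The strongest reply is that no sentence puts remission into the linear mixed model by name. Remission is defined on its own terms as a proportion, and a condensed article may leave the test for one binary outcome to a full protocol or analysis plan that is not shown. That would be a complete answer if the article were merely silent. It is not: the lead-in covers all secondary measures, and the baseline correction covers all analyses, with no exception. What stands is that the link is a literal reading, and that a fuller document may already resolve it.

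A reader might infer four stronger claims, which the documents do not support:

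- *That there is no valid analysis.* The empty term drops out and the remaining model estimates a risk difference with tolerable error rates.
- *That missing data are not handled.* A rule is stated: "No imputation of missing values will be performed", with available data used. The fair criticism is only that its reasoning is tied to the linear mixed model.
- *That a T0 row with zero variance breaks the model.* The article does not say that T0 is kept as an outcome row, and including one did not disturb the error rate in simulation.
- *That comorbid psychiatric disorders, an exploratory measure, share the problem.* They are binary, but *Participants* excludes only bipolar disorder and current psychosis. Other disorders may be present or absent at T0, so their baseline is not constant.

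It is also fair to say that the figures in Step 3 are hypothetical. With equal loss the risk ratio stays at 2.0 (0.32 / 0.16). They show the effect of a counting convention, not an error in the plan.

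**Conclusion.** The point holds in a limited form. Read literally, the article corrects remission for a baseline value that eligibility makes constant. The correction cannot be estimated, and remission goes unadjusted for baseline severity. The stated model fits a yes/no outcome poorly but is not void.

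The cost is precision. Its size cannot be given, because the documents do not say how strongly baseline HDRS predicts remission. The missing-status rule moves an assumed 20-point difference to 16 points with equal 20% loss, and to between 10 and 22 points with the unequal losses shown. These results rest on assumed remission rates and on inferring from the entry criterion that nobody is in remission at T0. The primary HDRS analysis and the sample size are untouched.

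**What to change.** Three changes of wording in *Efficacy analysis*:

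1. Limit the linear mixed model with baseline correction to continuous outcomes.
2. Analyse remission at T2 and at T5 with a logistic model, or with GEE over the post-baseline visits at which the SCID-I is done. Adjust for baseline HDRS and for season, the factor by which randomisation blocks are formed. Report the risk difference with its 95% confidence interval.
3. Add a sensitivity analysis in which a missing SCID-I status counts as not remitted, and state the denominator used.

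The cost is two or three sentences. No extra patients, visits or measurements are needed, since baseline HDRS and season are already recorded. One caution: at the assumed rates and 20% loss, about 42 × 0.8 × (0.40 + 0.20) = 20 remissions would be observed. The covariates should therefore be kept to these two, with a fallback named in advance in case the season terms cannot be estimated stably.
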